### Data management

All data will be encrypted, password protected, and kept in the cloud storage provided by the institution as well as principal investigator’s computer. All identifiable information will be removed and replaced by study code in all the working files. A master file with study code and protected health information (name, date of birth, and contact information) will be encrypted, password protected, and kept separately. All hard-copy research documents will be locked in a cabinet. Only approved research team members will have access to these restricted data sets.

### Sample size calculation

A previous study that used jogging as an exercise format in a group of children with ASD aged 5 to 13 years demonstrated that the percentage of time the participants spent in vigorous exercise, which correlates with engagement, was significantly higher under the slow-music condition (a tempo of 60, which is similar to the songs developed in this proposal) compared with the non-music condition (mean difference = 11.8%, common SD = 21.6%, effect size d = 0.55) [26]. Another study also revealed that music increased the engagement of students with autism during group activities [18], as the percentage of time in class during which participants exhibited active engagement behaviors increased from 44.7% ± 16.9% to 68.8% ± 13% (effect size d = 1.61). Considering these studies, assuming an effect size (d) of at least 0.55 in the primary outcome proposed for this study (engagement) will be observed for the Taekwondo training with elements of music therapy condition in contrast to the Taekwondo training alone condition, a minimum of 54 subjects are required to detect such an effect with a power of 80% and type I error of 0.05. To account for a 20% attrition rate and the requirement of pairing-up children for practice per group, 72 participants will be recruited in total.

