### Randomization and blinding

Block randomization will be implemented for this study, with varying block sizes of 2 to 4, to prevent selection bias and predictability. The randomisation list will be computer-generated and concealed by a researcher (author identifying information) who will have no direct contact with the participants. A research assistant will enroll participants and assign them to either the “Taekwondo training with elements of music therapy” (n = 36) or the “Taekwondo training alone” (n = 36) group in a 1:1 ratio. Given the behavioral nature of the intervention, blinding will not be feasible for the participants and parents. They will be unaware of their group allocation in the recruitment process until they provide written consent. The coaches, the trial coordinators, and the research personnel who review and code the video recording of the training sessions will also not be blinded to the group allocation. There will be concealment of the allocation sequence so that the trial coordinators will not know the group allocation of an individual before they consent them. To minimize measurement bias, all other research personnel involved in data collection, processing, and analysis will be blinded to group allocation.

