### Statistical analysis

The participants’ characteristics and primary and secondary outcomes will be evaluated using summary statistics, including mean (SD), median (IQR), or proportions as appropriate, at multiple time points. The primary analysis will consist of an intention-to-treat analysis comparing the primary outcome (engagement) between the two intervention groups; specifically, a linear mixed-effect model will be used to investigate the effect of intervention (Taekwondo training with vs without elements of music therapy) over time (interaction between intervention and time) on the engagement in the training sessions, with a random effect for each participant. The effects of music therapy on the secondary outcomes measured during the training sessions, including physical activity levels, enjoyment state, and the rate of perceived exertion, will be tested by independent samples t-tests. Further, we will use a linear regression model to investigate the effect of intervention on these outcomes, adjusting for the following prognostic variables: age, sex, and BMI. A log transformation will be applied for any outcomes resulting in a skewed distribution.

For the other secondary outcomes measured before and after the training sessions, a linear mixed-effect model will be used to investigate the effect of intervention over time (interaction between intervention and time), with a random effect for each participantand adjusting for the following prognostic variables: age, sex, and BMI. The analyses will also evaluate the sustained benefits of the training by assessing the effect of the intervention on the secondary outcomes at the 2-month follow-up using the statistical methods described above. The significance level will be set at *p*< .05, and all analyses will be performed using SPSS (v25.0 for Windows; IBM, Armonk, NY, USA).

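### The sample size is about half of what its stated inputs require: 54 children in total give about 51% power at d = 0.55, not 80%

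*Protocol article*

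**What the plan says.** The Sample size calculation section takes its planning effect from a jogging study in children with ASD ("mean difference = 11.8%, common SD = 21.6%, effect size d = 0.55"). It applies d of at least 0.55 to engagement, the primary outcome, for music versus no music, and states that "a minimum of 54 subjects are required to detect such an effect with a power of 80% and type I error of 0.05". It continues: "To account for a 20% attrition rate and the requirement of pairing-up children for practice per group, 72 participants will be recruited in total".

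The Study design section describes a parallel-group trial. The Randomization and blinding section allocates 36 children to each "group in a 1:1 ratio". The Statistical analysis section analyses engagement by intention to treat, in a linear mixed model with an intervention-by-time term and a random participant effect. The Intervention section gives 20 training sessions per child, in classes of six.

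The sample size paragraph names no formula and no sidedness. It uses no number of repeated measurements, within-child correlation, covariate gain or class effect.

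**The concern.** The contrast is between two separate groups of children, and the paragraph gives an effect size, a power and a type I error. Those inputs fix the number needed for a comparison of two means, and it is roughly twice the stated 54. The stated minimum is close to the number needed in each arm, which suggests that a per-arm figure was carried forward as the trial total.

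This is the trial's only sample size justification, and it concerns the primary outcome. If the power is far below the stated 80%, a non-significant result says much less about the music component than readers of a trial described as 80% powered would suppose.

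**Working it through.** **Inputs.** From Sample size calculation: d = 0.55 (11.8/21.6 = 0.546, rounded), power 80%, type I error 0.05, attrition 20%, 72 recruited. From Randomization and blinding: 1:1, 36 per arm. Sidedness is not stated, so both cases are shown.

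**Is 54 a total or a per-arm number?** 54/0.8 = 67.5. The next multiple of 12 (two arms of classes of six) is 72, which matches the recruited total. Had 54 been per arm, recruitment would have been 108/0.8 = 135. So 54 is used as a total, 27 per arm.

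**Attempt to reproduce 54.** For two independent means, n per arm = 2(z₁₋α/₂ + z₁₋β)²/d² = 2(1.960 + 0.842)²/0.55² = 51.9, so 52 per arm. The exact noncentral t gives 53 per arm, 106 in total. With the unrounded d = 0.546 it gives 54 per arm, 108 in total. A one-sided test at d = 0.55 needs 42 per arm, 84 in total. None of these gives 54 in total; 53 to 54 is the two-sided number per arm.

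**Power at d = 0.55** (noncentral t, noncentrality d√(n/2), 2n − 2 degrees of freedom, one value per child):

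| Children analysed | Per arm | Two-sided | One-sided | d with 80% power, two-sided |
|---|---|---|---|---|
| 54 (stated minimum) | 27 | 51% | 64% | 0.78 |
| 58 (72 less 20%) | 29 | 54% | 66% | 0.75 |
| 72 (no loss) | 36 | 63% | 75% | 0.67 |
| 106 | 53 | 80% | 88% | 0.55 |

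At the cited SD of 21.6 points, d = 0.75 is 0.75 × 21.6 = 16.2 percentage points, against the 11.8 on which the plan is based.

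**Shortfall.** 54/106 = 51% before attrition. After it, 106/0.8 = 132.5, so 134 for equal arms, and 72/134 = 54%.

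**What repeated sessions could do.** Suppose d refers to a single session, the analysis compares the mean of m sessions, sessions within a child are equally correlated at ρ, and there is no class effect. The variance is then multiplied by (1 + (m − 1)ρ)/m. Power reaches 80% when this factor is at most (0.55/d₈₀)², where d₈₀ is the last column of the table: 0.501 at 27 per arm, 0.540 at 29 and 0.675 at 36.

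| Sessions averaged | Largest ρ, 54 children | Largest ρ, 58 children | Largest ρ, 72 children |
|---|---|---|---|
| 3 | 0.25 | 0.31 | 0.51 |
| 5 | 0.38 | 0.43 | 0.59 |
| 20 | 0.47 | 0.52 | 0.66 |

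**What class effects could do.** The documents give no class ICC, so these values are assumptions. With classes of six the design effect is 1 + 5 × ICC. At 29 per arm, single-measurement power falls from 54% to 52% at ICC 0.01, 50% at 0.02, 45% at 0.05 and 38% at 0.10.

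**The case against.** The strongest reply is that the 51% belongs to a test that the plan does not use. The primary analysis is a mixed model over sessions, each child has 20 sessions, and sessions are to be video-coded. Averaging even a few of them can restore 80% power if the within-child correlation is modest. A child who leaves midway still contributes the sessions already coded, so the effective loss may be below 20% and the 58-child figures may be pessimistic. Other routes also reach about 54: covariance adjustment for a baseline correlated at about 0.7, or a repeated-measures formula with two uncorrelated measurements. The planning effect is also called a lower bound, and the other cited study gives d = 1.61.

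Part of this stands. The true power of the planned model cannot be known from the article, and 51% should be read as the single-measurement value. The per-arm-for-total slip is an inference; the match is close but does not prove it.

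It does not rescue the stated figure. Every route to 54 needs an input that the paragraph does not use, and a class effect would push the other way. The 80% claim is tied to d = 0.55, so a larger effect elsewhere is no support for it. Nor is this a detail that a condensed article may leave out: the paragraph gives both inputs and result, and the result does not follow.

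**Conclusion.** The concern holds. On the stated inputs the minimum is 106 children in total, not 54, and 54 children give about 51% power. The planned recruitment of 72 gives about 54% after the assumed attrition and 63% with none.

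These figures assume a two-sided test, one engagement value per child and no class effect. One-sided testing does not change the conclusion. Repeated sessions might, but only under correlations that the calculation does not state: over 20 sessions, about 0.47 or lower for 54 children and 0.66 or lower for 72, again with no class effect.

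**What to change.** Rewrite the sample size paragraph in one of two ways.

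1. Keep the single-measurement basis and give its true result: two-sided, 72 recruited and about 58 evaluable, about 54% power at d = 0.55, and 80% power for d of about 0.75.
2. Redo the calculation for the planned analysis. Say whether the target is the arm difference in mean engagement over sessions or the intervention-by-time interaction, because d = 0.55 describes a mean difference. State the number of sessions coded, the within-child correlation, a class ICC, the sidedness and how dropouts contribute, and report power over a plausible range of the correlations.

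In either case say whether each number is per arm or in total. The cost is one corrected paragraph in the protocol, and the same correction in the registry entry and results paper wherever the figure appears. The stated power becomes less favourable under the first option and may do so under the second. Neither needs further enrolment or changes the intervention.

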### Ethical approval

The study protocol was approved by the Human Subjects Ethics Subcommittee of the Hong Kong Polytechnic University (HSEARS20211117003-05) on 4 October 2023. All study procedures will be implemented in compliance with the Helsinki Declaration. Participants will enroll in the study on a voluntary basis. The research coordinator will explain the study and obtain written consent from parents before the study commences.

### Statistical analysis

The participants’ characteristics and primary and secondary outcomes will be evaluated using summary statistics, including mean (SD), median (IQR), or proportions as appropriate, at multiple time points. The primary analysis will consist of an intention-to-treat analysis comparing the primary outcome (engagement) between the two intervention groups; specifically, a linear mixed-effect model will be used to investigate the effect of intervention (Taekwondo training with vs without elements of music therapy) over time (interaction between intervention and time) on the engagement in the training sessions, with a random effect for each participant. The effects of music therapy on the secondary outcomes measured during the training sessions, including physical activity levels, enjoyment state, and the rate of perceived exertion, will be tested by independent samples t-tests. Further, we will use a linear regression model to investigate the effect of intervention on these outcomes, adjusting for the following prognostic variables: age, sex, and BMI. A log transformation will be applied for any outcomes resulting in a skewed distribution.

For the other secondary outcomes measured before and after the training sessions, a linear mixed-effect model will be used to investigate the effect of intervention over time (interaction between intervention and time), with a random effect for each participantand adjusting for the following prognostic variables: age, sex, and BMI. The analyses will also evaluate the sustained benefits of the training by assessing the effect of the intervention on the secondary outcomes at the 2-month follow-up using the statistical methods described above. The significance level will be set at *p*< .05, and all analyses will be performed using SPSS (v25.0 for Windows; IBM, Armonk, NY, USA).

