The insights provided by Srinivasan et al. (2014) and their conceptual framework implicate several causal links between music experiences and the development of language, communication, and social-emotional, behavioral, and motor skills in children with ASD [32]. In addition, Karageorghis’s (2016) theoretical model that addresses the antecedents, moderators, and consequences of music used in the exercise and sports domain [27,33] provided us with a framework for developing a model of combined music therapy and Taekwondo training to improve the physical and mental outcomes of children with ASD (S1 Fig). The predicted immediate effects observed during the exercise sessions include increased engagement and enjoyment, reduced perceived exertion, and increased physical activity level. The predicted overall benefits of Taekwondo training with elements of music therapy include improvements in gross motor skills, Taekwondo skills performance, attention, and social communication and behaviors.

Herein, we propose to test this hypothesis by conducting a randomized controlled trial to evaluate participating children in terms of the aforementioned study outcomes of a 10-week Taekwondo training program, with the presence or absence of music.

This trial has two objectives: (1) to examine the immediate effects of music therapy integrated into Taekwondo training sessions on the engagement and enjoyment during the training sessions in children with ASD; and (2) to examine the effects of a 10-week Taekwondo training program, with the presence or absence of music therapy, on the physical and mental outcomes in children with ASD. We hypothesize that the addition of musical elements specifically designed to match the rhythm and dynamic movement of the Taekwondo training will increase active engagement during the training sessions and provide extra benefits on physical and mental outcomes for children with ASD. The domains to be evaluated include the immediate effects during the exercise sessions of engagement (primary outcome), enjoyment, physical activity levels, and rates of perceived exertion, as well as the overall effects of the training program on gross motor skills, Taekwondo skill performance, executive function, and psychosocial functioning and behavioral problems.

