### Intervention

In both conditions, the participating children will attend 20 sessions of Taekwondo training. Except for the experimental manipulation (the presence or absence of music), children will receive the same level, skills, and duration of Taekwondo training across both conditions. The training will be administered in a group setting (six children per class), twice a week over 10 consecutive weeks. Each training session will last for 45 minutes and consist of warming-up exercises, hand movements, stance, foot movement techniques, a combination of stance and hand and foot techniques, and cool-down exercises. The teaching syllabus will follow the white belt (most junior) rank of the Taekwondo grading system. A qualified Taekwondo coach will conduct the training alongside a teaching assistant and two student assistants in each session.

In the Taekwondo training with elements of music therapy group, elements of music therapy will be incorporated into exercise training. Each piece of music will be tailor-made according to the rhythm, dynamic, tempo, duration, and associated feeling of a series of Taekwondo movements. For example, when forceful kicking is necessary, music with a rapid rhythm and strong, heavily accented beat will be applied. The music will serve to guide the motor patterns in a feedforward manner. The coaches will provide demonstrations that follow the tempo and rhythm of the specially composed music to guide the children in completing the Taekwondo movements. Short songs will also be composed, recorded, and played to accompany recurrent activities such as deep breathing and movement transitions. These short music pieces will offer cues to the children for recurrent activities and increase their success in effectively following the coach’s lead.

Teaching assistants will document attendance rate and any significant events during the study period. Participants who have been consistently absent will be contacted to investigate the reasons for their absence and to encourage regular attendance. If a participant drops out of the training sessions, they will still be invited to complete the post-training and 2-month follow-up assessments. All kinds of ASD-related concomitant trainings are permitted during the study period and information on these trainings will be recorded.

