#### 1. Immediate effects in the training sessions

*1*.*1 Engagement in the training sessions (primary outcome)*. Training sessions will be videotaped and coded. The direct observation component of the Revised Individual Child Engagement Record (ICER-R) system will be applied to record individual children’s engagement [35,36] during the training sessions. The ICER-R uses a 15-second momentary time sampling approach and involves the coding of types of engagement, the occurrence of interaction with partners (coach or peers), and whether the child was physically prompted. The types of engagement being coded at each 15-second interval are active engagement, passive engagement, active non-engagement, and passive non-engagement. Anecdotal information including emotional response was recorded during the observation for qualitative analysis. The mean inter-observer agreement is 83% for engagement, 88.7% for interaction occurrence, and 96.8% for interaction partner [35]. The engagement during the training session is expected to be the most sensitive to changes induced by music therapy, as the music is specifically designed to match the rhythm and dynamics of the Taekwondo movements. This is supported by two previous studies showing that incorporating musical elements into exercise training/activities significantly increased the engagement level in children with autism [18,26].

*1*.*2 Enjoyment state*. The Children’s Emotional Manifestation Scale (CEMS) will be used to assess the children’s emotional state at the end of each training session. Children will be asked to select which cartoon facial expression most represents their emotional state. The numbers obtained for each category are added together to obtain the total score. High scores indicate the manifestation of more negative emotional behavior. The interrater reliability coefficient of the CEMS is 0.96, and its internal consistency has an alpha coefficient of 0.92 [37].

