*2*.*5 Social responsiveness scale*, *second edition (SRS-2)*. This scale will be completed by the parents. It is a 65-item autism rating scale widely used for identifying a spectrum of deficits in reciprocal social behavior, ranging from absent to severe, based on observations of a child’s behavior in various social settings. Scoring is on a four-point Likert scale with five subscales (social awareness, social cognition, social communication, social motivation, and autistic mannerism) [46]. Higher T-scores correspond to poorer social functioning. The questionnaire has an internal consistency of 0.95 and an inter-rater reliability of 0.77 [47].

*2*.*6 Strength and Difficulties Questionnaire (SDQ)*. The questionnaire will be completed by parents. There are 25 items in the SDQ, which consists of five scales, each with five items, for assessing children’s mental health status in terms of emotional, conduct, hyperactivity, peer problems, and prosocial behavior [48]. The questionnaire has an internal consistency coefficient of 0.81 and a test-retest reliability coefficient of 0.86 [48].

*2*.*7 Clinical global improvement (CGI) score*. The CGI-I will be completed by parents to evaluate children’s functional changes in daily life after completion of the 10-week program, and at 2-month follow-up [49]. The CGI-I consisted of 12 questions developed by our research team, which are focused on all core symptoms of ASD and covered the following aspects: (1) motor functioning; (2) children’s capability to follow instructions; (3) social, communication, and language understanding and expression; and (4) children’s capabilities for attention shifting, attention to complete a task, attention to details, and imagination. The CGI-I is rated on a 7-point Likert scale ranging from 1 (very much improved) to 7 (very much worse since the initiation of intervention), with 4 representing no change. A lower score for each item of the CGI-I indicates more favorable outcomes. In addition to these 12 questions, we modified the CGI-I in this study to include a question asking parents about the overall rating of their child and an open-ended question that enables parents to report their observations of their child after participation in this program.

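### The primary analysis names the intervention-by-time interaction for engagement, but the objective, hypothesis and sample size concern a difference in level, and no music-free engagement baseline is described

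*Protocol article*

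**What the plan says.** The Statistical analysis section opens with a between-group comparison: "The primary analysis will consist of an intention-to-treat analysis comparing the primary outcome (engagement) between the two intervention groups". The same sentence then makes this specific as a linear mixed model, with a random effect per participant and this stated purpose: "investigate the effect of intervention (Taekwondo training with vs without elements of music therapy) over time (interaction between intervention and time) on the engagement". The interaction is the only effect it names.

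Under Immediate effects in the training sessions, the observational coding system "will be applied to record individual children’s engagement [35,36] during the training sessions", from video. The baseline, post-programme and 2-month assessments are introduced under Overall effects of the Taekwondo training program, and engagement is not listed there. The Intervention section states: "In the Taekwondo training with elements of music therapy group, elements of music therapy will be incorporated into exercise training". It describes no music-free lead-in.

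Objective 1, in the Introduction, is "to examine the immediate effects of music therapy integrated into Taekwondo training sessions on the engagement and enjoyment during the training sessions". The hypothesis in the same section is that music raises active engagement during sessions. The sample size rests on "assuming an effect size (d) of at least 0.55 in the primary outcome proposed for this study (engagement"), taken from music versus no-music comparisons. The other in-session outcomes (physical activity level, enjoyment, perceived exertion) are compared between arms by t-tests and then by adjusted regression.

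**The concern.** An intervention-by-time interaction suits an outcome that has a pre-treatment value, because arms that start equal and then separate produce an interaction. The programme-level outcomes have such a value. Engagement, as the text describes it, does not: the first coded session in the music arm is already a session with music. An effect that is immediate and then steady, which is what Objective 1 describes, gives the same arm difference at every session and hence no interaction.

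The trial's headline p-value could then be non-significant although music raises engagement throughout. A benefit that starts large and fades would give an interaction of negative sign, which could be misread as harm.

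**Working it through.** **The plan's own figures.** The effect size is 11.8 / 21.6 = 0.546, reported as 0.55. It is a mean difference between music and no-music conditions divided by an SD, so it is a difference in level. The stated minimum of 54 subjects does not reproduce as a total for a two-sided two-sample comparison at 80% power. That needs 52 per arm by the normal formula (104 in total) or 53 per arm by the t-test (106). A repeated-measures calculation with two measurements gives 54 only if the within-child correlation is set to 0, which the article does not state. This is a separate matter. What counts here is that the effect put into the calculation is a level difference.

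**What the interaction estimates.** Let D(s) be the arm difference at session s.
- The interaction asks whether D(s) varies with s.
- If D(s) = 0.55 SD at every session, D(s) − D(1) = 0 for all s. The interaction parameter is exactly zero, whether time is linear or categorical.
- The session-averaged contrast is the mean of D(s), here 0.55.

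**Inputs for the size.**
- From the article: d = 0.55, N = 54 (stated minimum), N = 72 (recruited), 1:1 allocation, 20 sessions held, alpha 0.05.
- Assumed: m = 2 to 20 coded sessions, within-child correlation ρ = 0.3 to 0.7, total SD 1, random intercept, equally spaced sessions, two-sided tests, no clustering by class.

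**Averaged contrast by formula.** The variance of a child's mean is ρ + (1 − ρ)/m, and the standard error of the arm difference is √(2 × variance / n), with n per arm. For m = 20 and ρ = 0.5 the variance is 0.5 + 0.5/20 = 0.525.
- N = 54: SE = √(2 × 0.525 / 27) = 0.197; 0.55 / 0.197 = 2.79; power ≈ Φ(2.79 − 1.96) ≈ 0.80.
- N = 72: SE = √(2 × 0.525 / 36) = 0.171; 0.55 / 0.171 = 3.22; power ≈ Φ(3.22 − 1.96) ≈ 0.90.

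Simulation with t-tests on child means gives 78% and 88%, in line with the formula.

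**Simulated rejection rates, constant 0.55 SD benefit, all m and ρ above.**

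| Test | N = 54 | N = 72 |
|---|---|---|
| Interaction (difference in slopes) | 4.5% to 5.5% | 4.0% to 5.9% |
| Arm difference averaged over sessions | 57% to 93% | 71% to 98% |

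**When the benefit grows (N = 54).**

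| Pattern | Sessions | Interaction | Averaged contrast |
|---|---|---|---|
| 0 rising to 0.55 SD | 3 | 39% to 72% | 20% to 28% |
| 0 rising to 0.55 SD | 20 | 90% to 99.9% | 22% to 39% |
| 0.275 rising to 0.55 SD | 3 | 13% to 25% | 38% to 52% |
| 0.275 rising to 0.55 SD | 20 | 37% to 69% | 43% to 71% |

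The interaction has good power only when the benefit starts near zero and builds over many coded sessions.

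**The case against.** The strongest reply is that the sentence begins as a comparison between the two groups. A model with arm, time and their product also yields an arm contrast, and nothing says the interaction p-value alone decides the trial. The opening phrase can indeed be read that way. But the interaction is the only effect named once the sentence becomes specific, and the two readings can give opposite conclusions. An unseen analysis plan might settle the choice; the protocol as published points to the interaction.

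Second, the lack of a pre-music engagement value is inferred. The schedule and assessment-flow figures are not shown, and the Abstract lists engagement among the outcome domains just after describing the pre, post and follow-up assessments. This caveat stands. Still, the measures section separates in-session outcomes from those assessed at baseline, and no text describes filming a music-free session.

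Third, a growing benefit is plausible, since the Introduction expects songs to become cues for the next movement. In that case the interaction does well and the averaged contrast poorly, as the second table shows. That supports keeping the interaction as a secondary question. It does not make it the test of an immediate effect.

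Fourth, the 5% figure holds by construction, and the power ranges rest on assumed correlations and numbers of coded sessions. Both are true, which is why ranges are given.

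**Conclusion.** The concern holds: the effect named as the primary test does not match the objective, the hypothesis or the effect used for sizing. If the benefit is constant, the named test is non-significant about 95% of the time at any sample size, against 57% to 93% power at N = 54 (71% to 98% at N = 72) for the averaged contrast. The mismatch rests on the text as it stands, with two figures not shown. The power ranges rest on the assumed m and ρ and ignore clustering in classes of six.

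Three stronger readings are tempting, and the document does not support them.
- A reader might infer that the CGI-I suffers the same fault, because parents rate "functional changes in daily life after completion of the 10-week program, and at 2-month follow-up" only. The second mixed model is stated for outcomes measured before and after training, which the CGI-I is not, so that sentence need not cover it.
- A reader might infer an inflated type I error from children having different trajectories. The article speaks of a random effect per participant without restricting it to an intercept, and gives no slope variability from which to size any inflation.
- A reader might take a single figure such as 88% as the power lost. That value needs 20 coded sessions, a correlation of 0.5 and no attrition, whereas the article plans for 20% attrition and does not say how many sessions are coded.

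**What to change.** State in the Statistical analysis section that the primary contrast is the between-arm difference in engagement averaged over the coded sessions, estimated from the same mixed model with session as a fixed factor. Write it as that averaged contrast, because with an interaction in the model a default arm coefficient may refer to one reference session only. Keep intervention-by-session as a secondary analysis of the time course. If a music-free engagement measurement is in fact scheduled, say so in the text.

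The cost is a wording change made before the data are analysed, with no new measurements. The downside is small: the time-course question becomes secondary, and a benefit that starts at zero and only builds would be detected less readily by the primary test.
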